**Figure 1. F1:**
[figure not shown]
Flow chart of participants through the proposed trial.

### 2.2. Participants

#### 2.2.1. Recruitment

All patients will be enrolled from the Traditional Chinese Medicine and Urology clinics of Shanghai Fourth People’s Hospital.

#### 2.2.2. Inclusion criteria

Patients will be enrolled upon meeting the following criteria:

Males of 45 years or older.BPH diagnosed upon digital rectal examination.The measured volume of the prostate ≥30 mL.The maximum urinary flow rate <15 mL/second.BPH patients are willing to participate in this study.Continuous intake of western medicines for 3 months or more.Moderate to severe BPH (IPSS score >8).

#### 2.2.3. Exclusion criteria

Patients will be excluded if they have one of the following conditions:

Cancer of the lower urinary tract, including prostate and bladder cancer in the past 5 years.Acute urinary retention in the past 4 weeks.Serious cardiovascular disorders (myocardial infarction, arrhythmia, unstable angina) in the past 6 months.Concerns about the procedures, like pain due to acupuncture.Calculi of the lower urinary tract, or bladder (unless completely recovered).Unfit to participate in the study by investigators.Use of other traditional or alternative medicines (including herbs and acupuncture) for over 1 month.Sexually transmitted diseases, like syphilis, gonorrhea.Congenital anomalies that affect urination.Trauma or surgery that affects the lower urinary tract.Upper urinary tract obstruction and other conditions that impair renal function.Incapable of communicating with investigators or giving the informed consent.

### 2.3. Interventions

In the conservative medical treatment group, α-blockers, 5α-reductase inhibitors, and phosphodiesterase type 5 inhibitors are prescribed by the investigators based on individual conditions. Acupuncture or moxibustion is not allowed in this group. Patients in this group will take conventional medicines. They will be explained how the medications work and their potential side effects.

In the combined therapy group, patients will receive simultaneous acupuncture and moxibustion. The moxa segment is burnt and attached to the acupuncture needle (see Fig. 2).

**Figure 2. F2:**
[figure not shown]
Diagram of warming acupuncture and moxibustion.

Acupoints include: Zhongji (RN 3), Qihai (RN 6), Shenshu (BL 23, bilateral), Shuidao (ST 28, bilateral), Pangguangshu (BL 28, bilateral). Qihai is 1.5 *cun* inferior to the umbilicus along the anterior midline. The acupuncture needle is inserted into the body with the tip reaching a depth of 1 to 1.5 *cun*. One *cun* is defined as the width of the 1st interphalangeal joint of the patient. Zhongji is 4 *cun* inferior to the umbilicus along the anterior midline. The needle reaches a depth of 0.5 to 1*cun*. Shuidao is 3 *cun* inferior to the umbilicus and 2 *cun* lateral to the midline. The needle tip reaches 1 to 1.5 *cun*. Shenshu is 1.5 *cun* lateral to the spine of the 2nd lumbar vertebra on the back. The acupuncture needle tip reaches a depth of 1 *cun*. Pangguangshu is 1.5 *cun* lateral and inferior to the spine of the 2nd sacral vertebra on the back. The acupuncture needle tip reaches 1 *cun*. When patients have a feeling of “Teh Chi”, such as heaviness, numbness, and swelling, the needles will be kept in situ and burning moxa attached to the end of the needle. The moxa will be changed after burning out until 60 minutes are reached. These patients will be treated with the combined therapy once a week for 18 consecutive weeks. Patients in the combined therapy group will be managed by an experienced TCM doctor. Patients receiving this treatment will be managed in the same room. Communication between these patients will not impact their adherence.

Before the trial starts, patients will be briefed on our design and they have the choice to join either of the group, but which is better is not known before completing this trial. Therefore, they will be assigned to the two groups in a ratio of 1:1 after this briefing. Patients are encouraged to complete the trial with good adherence. As stated above, patients in the same group will be managed in the same room to minimize the impact of the selection of their therapies.

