## 2. Study design and Methods

### 2.1. Design and setting

This RCT is a single-center, investigator-initiated study, aiming to examine the efficacy of combined therapy of acupuncture and moxibustion in treating BPH. This efficacy will be compared with that of conservative western medical treatments alone. A calculated number of 200 BPH patients will be enrolled from the Urology and the Traditional Chinese Medicine clinics of Shanghai Fourth People’s hospital. BPH patients will be randomly assigned to these two groups using a random number table in a ratio of 1:1. A block size of 4 will be generated using a computer, which ensures equal numbers of patients assigned to both groups at designated time intervals. Randomization will be stratified based on the severity of symptoms, where a total score of the baseline International Prostate Symptom Score (IPSS) <7 is considered mild, 8 to 19 moderate, and 20 to 35 severe. Written informed consent to participate in this study will be obtained from all patients. The process is shown in Figure 1.

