### 2.7. Randomization

Randomization will be conducted using a random number table to assign patients to the two groups. Firstly, block size of 4 will be generated by a computer and 200 patients will be randomly assigned to the two groups in a ratio of 1:1 after acquiring their written informed consent to join a group, which ensures equal numbers of patients assigned to both groups at designated time intervals. Patients of the mild, moderate, and severe categories will be assigned equally to the two groups.

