### 2.8. Blinding

In this trial, investigators who manage patients with acupuncture and moxibustion are unaware of the allocation of patients because they will be treated with other patients in the clinic. Investigators who assess these patients during the follow-up are also blinded. The statistician is also unaware of the allocation. But patients are aware of their allocation. To minimize the impact of patients’ awareness of their allocation, they will be managed at different time points so that they are unaware of the treatment options of the other group. For patients in the same group, they will be treated in the same room and no patients from the other group will be present.

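### Section 2.3 gives patients a choice of group and section 2.7 takes consent to join a group, which contradicts the random allocation that the protocol otherwise specifies and appears to intend

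*Protocol article*

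**What the plan says.** All references are to the protocol article.

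**Random allocation.** Section 2.1 (Design and setting) says "BPH patients will be randomly assigned to these two groups using a random number table in a ratio of 1:1", with computer-generated blocks of 4 and stratification by baseline IPSS category. Section 2.7 (Randomization) agrees: "Randomization will be conducted using a random number table to assign patients to the two groups". It repeats the block size and the 1:1 ratio, and says that the severity categories will be divided equally.

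**Choice of group.** In section 2.3 (Interventions), the last paragraph, after the acupoint description, says that "patients will be briefed on our design and they have the choice to join either of the group". It then notes that the better treatment will not be known until the trial ends, and draws the consequence that "they will be assigned to the two groups in a ratio of 1:1 after this briefing". It closes by saying that patients of one group are managed in the same room "to minimize the impact of the selection of their therapies".

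**Consent.** Section 2.1 says "Written informed consent to participate in this study will be obtained from all patients". Section 2.7 instead has assignment take place "after acquiring their written informed consent to join a group".

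**The concern.** Whether patients choose their group or are allocated to it at random is the most basic property of the design, and the article says both. The choice language is not confined to one phrase. It appears twice in section 2.3, and the consent wording in section 2.7 fits with it.

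What is at stake is who enters which arm. If a patient's preference decided his arm, preference and anything associated with it (prognosis, response to earlier medicines, expectation) would differ between arms at baseline. Several features make this more than a formality:

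- Recruitment is from a Traditional Chinese Medicine clinic as well as a urology clinic (sections 2.1 and 2.2.1).
- Entrants have already taken western medicines for at least 3 months (section 2.2.2), so they may well hold a view on continuing them.
- The primary outcome is a questionnaire that patients answer (section 2.4.1).
- The 18-week comparison is a Student's t test (section 2.9), which does nothing to correct for self-selection. The mixed model named there is meant for unevenly spaced visits and missing values, and would not correct for it either.

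**Working it through.** No figure in the plan settles this, so the main check is to compare the texts. Two short calculations follow.

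**Step 1: can the statements be reconciled?**

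- *Allocation rule.* Sections 2.1 and 2.7 let a random list decide the arm. Section 2.3 ("patients will be briefed on our design and they have the choice to join either of the group") lets the patient decide. The object of the choice is the group, not participation.
- *Consent.* Section 2.1 has consent to take part in the study, which is compatible with randomisation. Section 2.7 has consent to join a group before assignment, which presupposes that the group is already settled.
- *Sequence.* The next sentence of section 2.3 ("they will be assigned to the two groups in a ratio of 1:1 after this briefing") points to assignment by the trial. It does not contain the word random, and it does not say that the choice lapses.
- *Handling of a choice.* Nothing describes a preference arm, or any procedure to record or act on a stated choice.

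The operational detail is all on the side of randomisation. The choice wording has no procedure behind it, but it is not withdrawn.

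**Step 2: could choice deliver the specified blocks?**

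Assume that patients choose independently, each picking the combined therapy with probability p. The chance that a block of 4 splits 2:2 is 6 × p² × (1 − p)². This is largest at p = 0.5, where it is 6 × 0.25 × 0.25 = 0.375. With 200 / 4 = 50 blocks, at most 50 × 0.375 = 18.75, or about 19, would be expected to balance. The scheme in sections 2.1 and 2.7 requires every complete block to balance. The two rules therefore cannot both be carried out, even when preferences are evenly divided.

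**Step 3: can the bias be sized?**

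The documents give neither the share of patients who would act on a choice nor the effect of preference on IPSS. Any figure rests on assumptions. Two cases show how far the answer depends on them, with no true treatment effect and the 80 patients per group of section 2.6:

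- *Input from the plan:* standard error of the difference in SD units = √(2/80) = 0.158.
- *Case A, all in one direction (assumed):* a share f of 20% to 50% enters the arm it prefers, preference shifts reported IPSS by 0.5 SD, and the effects do not offset between arms. Bias = f × 0.5 = 0.10 to 0.25 SD, which is 0.10/0.158 = 0.63 to 0.25/0.158 = 1.58 standard errors. The two-sided rejection rate at 0.05 is then 0.097 to 0.352.
- *Case B, evenly split (assumed):* the shift comes from receiving one's preferred treatment, and preferences divide equally. Both arms gain the same amount, the bias is about zero, and the rejection rate stays near 0.05.

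The result runs from about 5% to about 35% on these assumptions alone, and nothing in the documents selects among them.

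**The case against.** The strongest reply is that section 2.3 describes an equipoise briefing in awkward English: patients hear that either group is possible and that neither is known to be better, and are therefore assigned 1:1. Read with the random number table, the blocks, the stratification, the consent wording of section 2.1 and the Discussion's description of the study as an RCT, this is probably what the authors meant. That stands. It limits the point to a contradiction in the text.

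It does not remove the point. The words are about which group to join, the paragraph later speaks of patients' selection of therapies, and section 2.7 has its own version of the same idea. Someone drafting a consent form from section 2.3 could fairly offer a choice.

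Three stronger readings are tempting, and the documents do not support them:

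- *The trial is a self-selected comparison.* Nothing shows that allocation is by choice. That consequence is conditional on the choice wording being followed.
- *The false-positive rate is 10% to 35%.* That is Case A of the working. It needs preference to act in one direction, and neither the share nor the shift comes from the documents.
- *The blinding section belongs to the same fault.* Section 2.8 says "they will be managed at different time points so that they are unaware of the treatment options of the other group", which sits uneasily with a briefing on the design. But it is explained there by separate times and rooms, and may mean only that patients do not see the other group's care. It is a separate matter and says nothing about how the arm is decided.

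It is also fair to say that patients who know their arm may stay in it, or report better scores, according to preference in any open-label trial. Correcting the choice wording leaves that risk in place. Only preference-driven entry into an arm belongs here.

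**Conclusion.** The point holds as an internal contradiction. The choice wording in section 2.3 and the consent wording in section 2.7 are wrong as written against the random, stratified, blocked 1:1 allocation in sections 2.1 and 2.7. It must be corrected, because a stated rule that would undo randomisation if followed should not stand in a trial protocol.

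Confidence is high that the texts conflict. It does not extend to how patients are in fact allocated, and the better reading is that randomisation is intended. If the choice wording were applied at enrolment, the 18-week comparison of a patient-reported outcome would no longer rest on randomisation. The size of that bias cannot be derived from the documents, and the verdict does not depend on it.

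**What to change.** 1. In section 2.3, delete the statement that patients may choose a group, and delete the reference to the selection of therapies. Keep the statements that the better treatment is unknown and that assignment is 1:1, and add that the assignment is random.
2. In section 2.7, replace consent to join a group with consent to be randomly assigned to either group, given before the allocation is known. Bring the consent form into line.
3. State that patients cannot choose their group, and that a patient who would not accept assignment to either one is not enrolled.

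The order of events needs no redesign. Section 2.7 already puts assignment after written consent, and stratifying by baseline IPSS already requires that score beforehand.

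The cost is a change of wording. A few patients with a strong preference may not be enrolled, although section 2.2.3 already excludes some of them through its criterion on concerns about the procedures. The sample size and the analysis do not change.

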### 2.4. Outcome measures

Primary and secondary outcomes will be evaluated by independent outcome assessors. They are well trained clinicians and familiar with these outcome measures and blinded to the randomization procedure. The primary outcome IPSS will be assessed using a questionnaire, secondary outcomes such as maximum flow rate (Qmax), post-voiding residual urine volume, and average flow rate (Qave), time to maximum flow, and voiding time will be measured through ultrasound examination at recruitment and 18 weeks after the trial starts. The evaluation results and time chart are as follows (Fig. 3).

**Figure 3. F3:**
[figure not shown]
Evaluation results and time chart.

#### 2.4.1. Primary outcomes

The IPSS at 18 weeks after the start of the trial will be used to assess the severity of symptoms and treated as the primary outcome. The IPSS has 8 questions with each of the first 7 questions scored 0 to 5, resulting in a sum of 0 to 35. These questions are about urinary symptoms for patients to tick one out of six answers. These include: frequency, incomplete emptying, intermittency, weak stream, urgency, straining, and nocturia. A total score of <7 is ranked mild, 8 to 19 moderate, and 20 to 35 severe. The 8th question is about the quality of life perceived by the patients, which ranges from 0 to 6, corresponding to delightful to terrible quality of life.

#### 2.4.2. Secondary outcomes

The volume of residue urine in the bladder will be measured through the ultrasound examination before and after treatment and this difference will be compared between groups.

The peak and the average urine flow rates will be calculated using the Qmax and the Qave collected from the urodynamic examination.

Voiding time, time to completely empty the bladder, and the time to maximum flow will be measured during the urodynamic examination.

### 2.5. Safety assessment

Adverse events will be closely surveilled during the treatment. If pain, bleeding, fainting, dizziness, and other symptoms occur, they will be recorded in the case report forms. They will be recorded even if these symptoms occur in patients’ houses. Responsible investigators will be immediately informed and appropriate measures taken after appropriate assessment of these patients. If the adverse events significantly impact the quality of life of these patients, they can withdraw from the study and medical care will be provided to them.

### 2.6. Sample size

To calculate the sample size, results of our pilot study were used to estimate the number of patients we need for this trial. In our RCT, the efficacy of the combined therapy and the conservative medical treatment was 80% and 60%, respectively, 0.05 for α, 0.8 for 1-β, 20% for the dropout during the follow-up. Eighty patients in each group are required as calculated using the Two Independent Proportions (Null Case) Power Analysis (Pass 11 software). A 25% dropout rate is estimated. Finally, 100 patients in each group are needed.

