### 2.9. Statistical method

Results collected will be initially validated by two investigators before statistical analyses. Data analysis will be conducted using IBM SPSS (version 20.0) for Windows (SPSS Inc., Chicago, IL) by a statistician who is blinded to patients’ information. Continuous variables will be presented as mean ± SD or median with an interquartile range (IQR). Information of patients at enrollment will be compared using the Mann-Whitney *U* test or using the *t* test for continuous variables, and the Fisher’s exact test or χ^2^ for categorical variables. Two-side Student’s *t* test will be used to compare continuous variables like IPSS, maximum flow rate, voiding time, average flow rate, post-voiding residue urine volume, and time to maximum flow 18 weeks after treatment. Longitudinal analysis of IPSS, Qmax, voiding time, post-voiding residual urine, Qave, and time to maximum flow were done with a GLMM approach, accommodating data with nonequidistant repeated measures of time and missing values. *P* < .05 (two-sided) is considered statistically significant.

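### The 80% power in section 2.6 belongs to a comparison of two efficacy proportions that the trial does not plan; power for the 18-week IPSS t test is not established

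*Protocol article*

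**What the plan says.** Section 2.6 bases the sample size on pilot results: "the efficacy of the combined therapy and the conservative medical treatment was 80% and 60%, respectively". The error rates and dropout are given as "0.05 for α, 0.8 for 1-β, 20% for the dropout during the follow-up". The method and result follow: "Eighty patients in each group are required as calculated using the Two Independent Proportions (Null Case) Power Analysis (Pass 11 software". After a dropout allowance the section ends with "Finally, 100 patients in each group are needed".

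Section 2.4.1 names a different quantity as the primary outcome: "The IPSS at 18 weeks after the start of the trial". This is a sum score from 0 to 35. The severity bands given there describe the patient's state and are not a rule for treatment response. The secondary outcomes in sections 2.4 and 2.4.2 are residual urine, peak and average flow, voiding time and time to maximum flow, all continuous.

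Section 2.9 treats IPSS as continuous. A two-sided Student's t "test will be used to compare continuous variables like IPSS" and the secondary measures at 18 weeks. The same section adds a longitudinal GLMM for these variables and does not say which of the two analyses is primary. Chi-square and Fisher tests are named only for comparing patients at enrolment.

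**The concern.** The article states its sizing basis, its primary outcome and its test, and the first does not fit the other two. The 80% and 60% are rates of a binary variable that the trial neither lists nor tests. No IPSS difference and no IPSS standard deviation enter the calculation, so the 0.8 is not a property of the comparison on which the trial will be judged.

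Two things are at stake. The calculation is the article's stated justification for enrolling 200 men, and it does not show what IPSS difference the trial is built to find. Also, an efficacy rate that appears only in the planning section leaves room for a responder rule to be chosen once the data are in.

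**Working it through.** **Inputs from the article.** Rates 0.80 and 0.60, α = 0.05, power 0.80, 80 per group before dropout and 100 after (section 2.6); 1:1 allocation (section 2.1); two-sided testing (section 2.9). **Not in the article:** an IPSS difference or SD. All values of these below are assumptions.

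**Step 1. Reproduce the 80 per group.** With z(0.975) = 1.960, z(0.80) = 0.842 and mean rate 0.70:

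- Pooled: n = [1.960·√(2·0.7·0.3) + 0.842·√(0.8·0.2 + 0.6·0.4)]² / 0.20² = 81.2, so 82.
- Unpooled: n = (1.960 + 0.842)²·(0.16 + 0.24) / 0.04 = 78.5, so 79.
- Exact binomial enumeration of the pooled z test: power 0.795 at 79 and 0.801 at 80.

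The stated 80 is therefore right for a two-sided comparison of two proportions. With 20% dropout, 80/(1 − 0.20) = 100. (The section also says "A 25% dropout rate is estimated", and 80/(1 − 0.25) would be 107. That is a separate matter.)

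**Step 2. What 80 evaluable per group gives the t test.** By normal approximation the standardized difference detectable with 80% power is (1.960 + 0.842)·√(2/80) = 0.443. With the t distribution it is 0.446. In points, 0.446 × SD:

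- SD 5: 2.2 points
- SD 6: 2.7 points
- SD 7: 3.1 points

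With 75 evaluable per group (25% dropout from 100) the normal approximation moves only from 0.443 to 0.457.

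**Step 3. Power of the t test at 80 per group, and n per group for 80% power.** Two-sided 5%, noncentral t:

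| Assumed difference | Assumed SD | Power at 80 | n for 80% power |
|---|---|---|---|
| 2 points | 5 | 71% | 100 |
| 2 points | 6 | 55% | 143 |
| 2 points | 7 | 43% | 194 |
| 3 points | 5 | 96% | 45 |
| 3 points | 6 | 88% | 64 |
| 3 points | 7 | 77% | 87 |

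**Step 4. Could the 80%/60% be carried over to the t test?** Only with a further assumption. Suppose efficacy meant passing a cut-off on a normally distributed IPSS response with equal SDs. The implied shift is z(0.80) − z(0.60) = 0.842 − 0.253 = 0.588 SD. The t test would then have about 96% power at 80 per group, and 47 per group would give 80%. The article states no such cut-off.

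These figures apply to the 18-week t test only, not to the GLMM.

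**The case against.** The strongest reply is that no harm has been shown. The one scenario built from the article's own rates (step 4) puts the t test at about 96%, above the target. A completed trial is in any case read from its estimate and confidence interval, not from its planned power. The article is also condensed, and the full protocol may define efficacy.

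Much of this stands. A reader might infer that the trial is underpowered, or that the 80% is numerically wrong for the t test. The documents support neither: without an IPSS difference and SD, power for that test is undetermined, and step 3 shows values on both sides of 80%. By the same token, step 4 is no reassurance, because its cut-off is assumed.

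A reader might also infer that an assumed advantage of 20 percentage points contradicts the aim of showing comparable effectiveness. It does not do so outright. Section 1.1 hypothesises that the combined therapy is equal to, or better than, western treatment, and the assumed advantage fits the second possibility. The lack of a margin for the first is a separate question.

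The condensed format does not remove the mismatch. A definition of efficacy held elsewhere would explain the 80% and 60%. It would not turn a two-proportion calculation into the power of a t test on mean IPSS, and the outcome list and test are stated in the article itself.

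**Conclusion.** The point holds as a mismatch between the sizing calculation and the planned primary comparison. The 80 per group is correctly computed, but for a test that is not among the planned efficacy analyses. For the IPSS t test the stated 0.8 is unsupported, which is not the same as shown to be too high or too low.

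The firm result is that 80 evaluable per group give 80% power for 0.446 SD. The 2.2 to 3.1 points and the 43% to 96% range depend on assumed SDs of 5 to 7 and, for the range, assumed differences of 2 to 3 points. The 96% under a dichotomised normal response depends on an assumption the article does not make. All of this takes the 18-week t test as the primary analysis, a reasonable reading of sections 2.4.1 and 2.9 that section 2.9 does not confirm.

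**What to change.** Rewrite section 2.6 for the 18-week IPSS t test:

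- Insert the IPSS SD from the pilot study. State the difference that 80 evaluable per group detect with 80% power at two-sided 5% (about 0.45 SD), converted to points.
- Set this beside the IPSS difference the sponsor considers relevant, with its justification, and report the power for that difference even if it is below 0.8. Whether 200 patients suffice follows from this comparison and should not be presumed.
- Do not work a non-inferiority margin backwards from the sample size. If one is wanted, it needs its own justification.
- If the 80%/60% rate is kept, define it in advance as an IPSS responder rule and list it as a secondary outcome with a two-proportion test.

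The work is one rewritten paragraph from pilot data the sponsor says it has, plus one outcome definition if the rate stays. The downside is that the stated power may become less favourable.

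### The sample size paragraph gives two dropout rates, 20% and 25%; 100 per group leaves the required 80 only at 20%, and at 25% the stated 80% power is not reached

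*Protocol article*

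**What the plan says.** Section 2.6 (Sample size) sizes the trial on a binary efficacy rate taken from a pilot study: "the efficacy of the combined therapy and the conservative medical treatment was 80% and 60%, respectively". The other inputs are "0.05 for α", a power of 0.8, and "20% for the dropout during the follow-up". The result before allowing for losses is given as "Eighty patients in each group are required as calculated using the Two Independent Proportions (Null Case) Power Analysis". The paragraph then ends: "A 25% dropout rate is estimated. Finally, 100 patients in each group are needed". The abstract and sections 2.1 and 2.7 carry the total of 200 forward. None of them mentions a dropout rate, so nothing elsewhere in the article settles which of the two applies.

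**The concern.** One paragraph gives two values for the same quantity, and the later one stands directly before the final sample size as if it led to it. A reader who takes 25% as the planning figure finds that 100 per group does not leave the 80 per group that the paragraph says are required. The plan would then claim a power that its own loss estimate does not support. A reader who takes 20% finds the sample size correct and the 25% unexplained. As written, it is unclear whether the trial is sized to absorb the loss of 20 or of 25 patients per group.

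**Working it through.** **Inputs.** From section 2.6: proportions 0.80 and 0.60, α = 0.05, power 0.80, dropout 20% and then 25%, 80 per group before dropout, 100 per group after. From section 2.9: two-sided testing ("< .05 (two-sided) is considered statistically significant"). From section 2.1: allocation 1:1.

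**Step 1. Reproduce the 80 per group.** The difference is 0.20 and the mean proportion 0.70, so 2 × 0.70 × 0.30 = 0.42 and 0.80 × 0.20 + 0.60 × 0.40 = 0.40.

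- Pooled variance: n = (1.960·√0.42 + 0.842·√0.40)² / 0.20² = 81.2, so 82.
- Unpooled variance: n = (1.960 + 0.842)² × 0.40 / 0.20² = 78.5, so 79.
- Exact enumeration of the two-sided pooled z-test at 80 per group: power 80.1%.

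The stated 80 is therefore sound for a two-sided test without continuity correction. Other variants do not give it: two-sided with continuity correction needs 91; one-sided needs 64 (pooled), 62 (unpooled) or 74 (with continuity correction).

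**Step 2. Allow for dropout.** If a fraction d is lost, the number to enrol is n/(1 − d).

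- d = 0.20: 80/0.80 = 100 per group. This matches the plan.
- d = 0.25: 80/0.75 = 106.7, so 107 per group and 214 in total. This does not match.
- The plan's 100 comes out of 25% only as 80 × (1 + 0.25) = 100. That is the correct step for a 20% dropout, but not for a 25% dropout.

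In the other direction: 100 × 0.80 = 80 evaluable per group, and 100 × 0.75 = 75.

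**Step 3. Power at 75 per group.** With the pooled formula, power = Φ[(0.20 − 1.960·√(0.42/n)) / √(0.40/n)]. At n = 75 this is Φ[(0.20 − 0.1467)/0.0730] = Φ(0.730) = 76.7%. With the unpooled formula, power = Φ[0.20/√(0.40/n) − 1.960]. At n = 75 this is Φ(2.739 − 1.960) = Φ(0.779) = 78.2%.

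| Two-sided 5%, 80% vs 60% | 80 per group | 75 per group |
|---|---|---|
| Pooled formula | 79.4% | 76.7% |
| Unpooled formula | 80.7% | 78.2% |
| Exact, pooled z-test | 80.1% | 76.8% |
| Exact, unpooled z-test | 80.2% | 78.4% |

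Losing five evaluable patients per group costs about 2 to 3 percentage points. At 75 per group every version is below 80%.

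**The case against.** The strongest reply is that nothing is underpowered and a label is wrong. Adding 25% to 80 is the same operation as allowing for 20% dropout, since 80 × 1.25 = 80/0.80 = 100. On this reading the 25% is the add-on, the 20% is the dropout, and 100 per group and 200 in total stand throughout the article. This is plausible and probably what happened. It does not clear the text, because section 2.6 calls the 25% a dropout rate, but it does make the power shortfall conditional on 25% being the real expectation.

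It is also fair to say that the shortfall is small, and that part of the distance from 80% depends on the formula: the pooled version gives 79.4% even at the planned 80. The power in section 2.6 also concerns a binary efficacy rate, whereas the primary outcome is the IPSS at 18 weeks, compared by t test. The figure of about 77% therefore says nothing direct about the primary comparison. That mismatch is a separate matter and does not make the two dropout rates agree.

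A one-sided test would not remove the problem. It does not reproduce the 80 per group, and section 2.9 specifies two-sided testing.

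**Conclusion.** The point holds. Section 2.6 contradicts itself on dropout, and only the 20% figure is consistent with going from 80 to 100 per group. If 25% is the true expectation, 75 per group remain and power is about 77% (up to 78% with the unpooled formula) against the stated 80%; keeping 80 evaluable would take 107 per group. These figures assume 80% versus 60%, a two-sided 5% level, 1:1 allocation and no continuity correction, and they apply only to the binary comparison used in that section. The effect is modest and does not threaten the trial, but the figures that justify the sample size should be put right.

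**What to change.** In section 2.6, give one dropout rate and show the division. The simplest correction is to replace 25% with 20% and write 80/(1 − 0.20) = 100 per group, 200 in total. This costs one figure and changes nothing in the design.

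If 25% is the loss actually expected, remove the 20%, keep 100 per group, and state that 75 evaluable patients per group are expected, with power of about 77% for the binary efficacy comparison under the section's own assumptions. The cost is a slightly less favourable stated power and no extra patients. Enrolling 107 per group, 14 more in total, would be needed only if the sponsor expects 25% and also wants to keep the full 80 evaluable per group.
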